### Beliefs about the consequences of ecstasy and NED use

Beliefs about the consequences of ecstasy and NED use will be measured using items adapted from the Project ALERT questionnaire [38]. To elicit perceptions about the social consequences of using ecstasy and NEDs, students will be asked about the positive and negative expectancies of using these drugs, for example, *‘using ecstasy and emerging drugs makes you feel more confident’.* Responses will be made on a four-point Likert scale labelled ‘strongly agree’, ‘sort of agree’, ‘sort of disagree’ and ‘strongly disagree’.

### Normative beliefs

To measure normative beliefs, students will be asked to estimate the proportion of their peers that use ecstasy and NEDs. Participants will also be asked three items adapted from the Project ALERT questionnaire [38], which aim to measure peer tolerance about ecstasy and NED use. For example, students will be asked to anticipate their friends’ reactions if they *‘found out you used ecstasy or emerging drugs sometimes’* (1 = ‘they would disapprove and stop being my friends’ to 4 = ‘they would approve’). Students will also be asked to indicate how strongly they agree or disagree with three statements relating to perceptions of the legality and safety of NEDs.

### Mental health outcomes

Psychological distress will be measured using the *Kessler 6* scale [39], a six-item questionnaire that measures depressive and anxiety symptoms in the past four weeks. The 25-item *Strengths and Difficulties Questionnaire*[5] will be used to measure both positive and negative attributes of students.

### Peer pressure

Peer pressure resistance will be measured using Bandura’s *Resistive Self-regulatory Efficacy scale*[40]. This scale consists of nine items that ask students to rate how well they can resist peer pressure to engage in different behaviours e.g. ‘*How well can you resist peer pressure to use pills (ecstasy)’.* Responses are made on a seven-point scale ranging from ‘Not well at all’ to ‘Very Well’.

### Parental monitoring

Students will be asked *‘Do your parents know where you are if you go out in the evening?’ and ‘Do your parents know whom you meet if you go out in the evening?’* and to make a response on a five-point scale ranging from ‘Yes, always’ to ‘No, never’. These items are commonly combined to provide an indicator of parental monitoring [41].

### Peer deviance

Five items adapted from a study by Svensson [41] will be used to measure relations with deviant peers. Students will be asked whether they have a friend who engages in deviant behaviour, for example, ‘*do you have a friend who has stolen something from a store?’ ,* and to make a Yes/No response.

### Program evaluation and implementation fidelity

Students that receive the *Climate Schools* intervention will be asked to complete an online evaluation questionnaire at the end of the final cartoon lesson. Teachers will also be asked to complete an online questionnaire at the conclusion of the program. To monitor adherence to the intervention, teachers will be required to complete a fidelity logbook at the end of each lesson via an online survey. The logbooks ask teachers to indicate which lessons and activities they completed with their class and to write down any factors that may have disrupted or impeded delivery of program. To ensure complete and consistent delivery of the online component of the intervention, the study website has been programmed so that students will be required to view the *Climate Schools* lessons in full before being granted access to the following lesson.

### Statistical analysis

Single-level analyses; one-way analyses of variance (for normally distributed data), Chi-square (for binominal data), and Mann–Whitney U-test (for non-normally distributed data) will be used to examine baseline equivalence and attrition between groups. Due to the multi-level and hierarchical nature of the data, mixed effects regression will be used to examine intervention by time interaction effects. To account for intracluster variance within schools, intervention effects will primarily be examined using hierarchical linear modelling (HLM) for normally distributed data and hierarchical generalized linear modelling using a Poisson distribution for count data. Outcome variables will be centred at post-test to allow for comparisons between groups immediately after the intervention, and growth terms will be analysed to determine the magnitude of the follow-up effects. Analyses will be conducted using the program Stata. If unconditional models reveal that less than 10% of systematic variance exists between school level for any outcome variable, HLM will be abandoned and single-level analyses will be used [4]. For these variables, ANCOVAs utilising the SPSS GLM procedure will be conducted to account for any baseline differences that might exist between groups. For multiple comparisons Bonferroni adjustments will be made. Effect sizes, odds ratios and 95% confidence intervals will also be calculated.

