### Study design

A cluster RCT will be conducted in 12 secondary schools in the greater Sydney region between 2014 and 2016. Six schools will be randomly assigned to the C*limate Schools* intervention group, and six schools to the control group. Cluster randomisation will be employed in this study to avoid contamination of the control group by the intervention group through student communication [34]. To evaluate the *Climate Schools* intervention for efficacy, students in both groups will complete five online self-report questionnaires over the three year study period. The trial has been approved by the University of New South Wales Human Research Ethics Committee (HREC HC13075).

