### Sample size calculations

To account for cluster randomisation, sample size calculations are based on recent sample size requirements developed by Heo and Leon [35] to detect intervention by time interactions in longitudinal cluster randomized clinical trials. To detect differences between groups, five schools (with an average of 75 students each) will need to be randomly allocated to receive the *Climate Schools* intervention, and five schools to a control group. Based on a recent school-based trial conducted by the investigators [33], in which there was an average of 125 students per grade in Sydney secondary schools, recruiting 75 students per school appears feasible. This will achieve 80 per cent power to detect a standardized between-group mean difference of 0.20 (p = 0.05) in outcomes at the end of the trial with three measurement occasions. An effect size of 0.20 for use is comparable to previous trials of universal drug prevention programs [19,27]. To account for school dropouts during the trial, which we expect to be approximately 10 per cent [28], we aim to recruit at least 12 schools, providing a minimum of 900 students at baseline to test the effect of the intervention in the overall group.

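### The baseline and attrition comparisons use single-level tests although schools are randomised, so their p-values ignore clustering; the attrition test matters most

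*Protocol article*

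**What the plan says.** The Study design section makes the school the unit of allocation: "A cluster RCT will be conducted in 12 secondary schools in the greater Sydney region between 2014 and 2016", with six schools assigned to the intervention "and six schools to the control group". The Sample size calculations section takes an average of 75 students per school, expects roughly 10% of schools to drop out, and so plans for at least 12 schools and 900 students.

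The Statistical analysis section begins with the baseline and attrition comparisons. It opens "Single-level analyses; one-way analyses of variance (for normally distributed data", goes on to name chi-square for binary data and Mann–Whitney for non-normal data, and says that these "will be used to examine baseline equivalence and attrition between groups". The next sentence acknowledges the clustering, but only for intervention effects: "Due to the multi-level and hierarchical nature of the data, mixed effects regression will be used" for the intervention-by-time interactions.

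Two later statements might seem relevant. One is a rule that drops hierarchical modelling for any outcome variable with under 10% of variance between schools. The other is a general statement that Bonferroni adjustment will be made for multiple comparisons. Neither adds a cluster adjustment to the baseline or attrition tests.

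**The concern.** Students in one school share an arm and tend to resemble each other, so 900 students do not supply 900 independent observations for a between-arm comparison. A test that assumes they do uses a standard error that is too small. The protocol fixes such tests by name, so this is a stated rule rather than a detail left to a fuller plan.

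The Outcomes section collects demographic data in order to judge whether the groups were comparable at baseline, and the attrition tests serve the same kind of statement about losses. With an inflated error rate, the report could announce an imbalance or differential loss that is no more than ordinary variation between schools. Attrition is the more exposed of the two. The protocol expects whole schools to leave, and surveys are completed in class under the teacher's direction, so missed surveys could also cluster by school without any school leaving.

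**Working it through.** **Inputs from the protocol article.** 12 schools, 6 per arm (Study design); 75 students per school, school dropout about 10%, significance level 0.05 (Sample size calculations). The totals agree: 12 × 75 = 900, and 10 schools / (1 − 0.10) = 11.1, which rounds up to 12. The protocol gives no figure for the error rate of the baseline or attrition tests, so there is none to reproduce.

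**Assumptions.** The ICC is not stated; a range of 0.001 to 0.10 is used. Schools are taken as equal in size and tests as two-sided.

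**Step 1: true size of a nominal 5% single-level test.** The design effect is DE = 1 + (75 − 1) × ICC. With no true arm difference, the single-level statistic is approximately normal with variance DE instead of 1, so

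true size = 2 × [1 − Φ(1.96 / √DE)].

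| Assumed ICC | DE | 1.96/√DE | True size |
|---|---|---|---|
| 0.001 | 1.07 | 1.89 | 5.9% |
| 0.01 | 1.74 | 1.49 | 13.7% |
| 0.02 | 2.48 | 1.24 | 21.3% |
| 0.05 | 4.70 | 0.90 | 36.6% |
| 0.10 | 8.40 | 0.68 | 49.9% |

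**Step 2: simulation check.** 12 schools of 75 students were simulated with no arm difference: 4,000 runs for ANOVA, chi-square (20% attrition assumed) and a t test on school means, and 2,000 for Mann–Whitney.

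| ICC | ANOVA | Mann–Whitney | Chi-square | t test on school means |
|---|---|---|---|---|
| 0 | 5.6% | 5.9% | 5.2% | 5.4% |
| 0.01 | 14.3% | 13.7% | 13.8% | 4.8% |
| 0.02 | 22.0% | 21.4% | 21.5% | 5.4% |
| 0.05 | 37.0% | 37.2% | 36.9% | 5.1% |
| 0.10 | 51.0% | 49.7% | 52.5% | 5.0% |

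All three planned tests are affected alike and match the formula. The school-level t test stays near 5%.

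**Step 3: does Bonferroni help?** It lowers the threshold but leaves the standard error wrong. With 10 tests the threshold is 0.005, and the true size is 3.3% at ICC 0.01, 7.5% at 0.02 and 19.5% at 0.05.

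**Step 4: several baseline variables.** The Outcomes section lists five (gender, age, religion, academic performance, truancy). If they were independent and all had ICC 0.02, the chance of at least one false signal without Bonferroni would be 1 − (1 − 0.213)^5 = 70%, against 1 − 0.95^5 = 23% for valid tests. This is an illustration; the documents support neither the common ICC nor the independence.

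**Step 5: loss of one school.** Ten per cent of 12 schools is 1.2, so about one. Suppose one school of 75 leaves one arm and nobody leaves the other, and its students count as lost.

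- Single-level chi-square on 75/450 vs 0/450: 900 × (75 × 450)² / (75 × 825 × 450 × 450) = 81.8, p about 1e-19.
- Fisher's exact test on schools, 1/6 vs 0/6: p = 1.0.
- t test on school proportions: the difference is 1/6. The within-arm variances are 1/6 and 0, pooled 1/12, so the standard error is √(1/12 × 2/6) = 1/6. Then t = 1.0 on 10 df, p about 0.34.

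One event at one school, of a kind the plan anticipates, would be reported as overwhelming evidence of differential attrition.

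**The case against.** The strongest reply is that little hangs on these tests. They are supporting checks, and intervention effects are to be examined primarily by hierarchical models. The error runs towards false alarms, not towards hiding a problem or creating a claim of efficacy. After proper randomisation a baseline difference is due to chance in any case, so even a cluster-adjusted baseline p-value says little. All of this stands. It limits the importance of the point and shifts its weight to attrition, where the cause of a difference is a real question.

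The ICC is also unknown. At 0.001 the inflation is trivial (about 6%), so the size of the problem is conditional. Bonferroni, if meant to cover these tests, would reduce the count of false signals: with five tests at 0.01 and ICC 0.02, to about 42% for at least one, against 4.9% for valid tests. That is still far from valid.

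Three stronger readings are tempting but not supported.

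- A reader might infer that false baseline signals will drive covariate adjustment, because the section speaks of accounting for baseline differences. That phrase belongs to the ANCOVA fallback for outcomes with under 10% school-level variance. Nothing says that the baseline tests select covariates.
- A reader might call attrition the main threat to the trial. The protocol gives no student attrition rate and does not say this.
- A reader might refer the single-level statistic to a t distribution on 10 df and obtain larger sizes (17% to 51% for ICC 0.01 to 0.10). That reference is wrong here: at ICC 0 it gives 7.8%, where the test has its nominal 5%.

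**Conclusion.** The point holds in a limited form. The named tests do not match the unit of randomisation, and neither the 10% variance rule nor Bonferroni repairs them. With 75 students per school, the inflation is slight at an ICC of 0.001, nearly threefold at 0.01 (about 14%), and reaches about 37% to 50% at 0.05 to 0.10. These figures rest on the assumed ICCs and equal school sizes; the one-school example also assumes that students of a departed school are counted in the attrition test, which the protocol does not settle.

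The consequence is wrong statements about differential attrition or baseline imbalance. It is not a direct inflation of the efficacy type I error. The plan should be changed on this point, mainly for attrition, but the point does not by itself put the efficacy analysis in doubt.

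**What to change.** In the first sentence of the Statistical analysis section, replace the single-level tests.

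- **Attrition:** at each wave, compare arms with a t test on school proportions (10 df with all 12 schools), or with a mixed logistic model that has a school random intercept and a small-sample correction. With 12 schools, the mixed model without that correction may itself reject too often. Only the school-level t test was checked here, on simulated school means of a continuous variable.
- **Whole-school loss:** report it separately, as schools lost per arm, so that it is not mixed with the loss of individual students.
- **Baseline balance:** report means or percentages by arm with standardised differences, and either no p-values or cluster-adjusted ones only.

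The cost is revised wording and a little more analysis work. The p-values will be less extreme, and neither the design nor data collection changes.

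### With 10 to 12 schools the primary hierarchical models need small-sample inference: tested against a normal reference, a school-level contrast would have 7.8% to 11.8% true error at a nominal 5%

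*Protocol article*

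**What the plan says.** Study design sets the number of clusters: "A cluster RCT will be conducted in 12 secondary schools in the greater Sydney region between 2014 and 2016", with six in each arm. Sample size calculations gives the minimum: "five schools (with an average of 75 students each) will need to be randomly allocated" to the intervention and the same number to control. Twelve are recruited because of expected losses: "To account for school dropouts during the trial, which we expect to be approximately 10 per cent".

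Statistical analysis names the primary method: "To account for intracluster variance within schools, intervention effects will primarily be examined using hierarchical linear modelling (HLM) for normally distributed data", with a Poisson version for counts. It adds that "mixed effects regression will be used to examine intervention by time interaction effects". The time origin is placed at the post-test survey so that the arms can be compared directly after delivery, and growth terms describe the follow-up effects. The section also fixes Stata, Bonferroni adjustment, 95% confidence intervals, and a rule that drops the hierarchical model for any outcome with less than 10% of its variance between schools. It states neither ML nor REML, neither a z nor a t reference, no degrees-of-freedom method and no random-effects structure.

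**The concern.** Treatment is assigned to schools, so the information on a school-level arm contrast comes from 12 school means less two arm means: 10 degrees of freedom, or 8 if only 10 schools remain. A large-sample normal test treats the between-school variance as known. With so few schools it is poorly estimated, and ML also biases it downwards. Both effects make intervals too narrow and p-values too small.

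At stake is the type I error of the primary comparisons. There are three primary outcome domains (knowledge, intentions, use), so per-test inflation carries into the trial's overall conclusion. Intervals labelled 95% would cover about 88% to 92%.

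**Working it through.** **Inputs from the article.** k = 12 schools, 6 per arm; floor of 10; 75 students per school; significance level 0.05 (sidedness not stated, taken as two-sided). **Assumed.** The ICC, which the article does not give; Gaussian outcomes; equal school sizes.

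**The plan's own figures.**
- School count: 5/(1 − 0.10) = 5.6, rounded up to 6 per arm, or 12. This reproduces. Expected survivors are 12 × 0.9 = 10.8, so 10 is the required minimum and not the expected count.
- Power of 80%: ignoring clustering, 5 × 75 = 375 per arm gives 78.2% for a difference of 0.20 SD. An intervention-by-time slope formula over three occasions with random intercepts gives 79.8% at a within-student correlation of 0.52. That correlation is not stated, so 80% is reachable but cannot be confirmed.

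**Size of a 1.96 cut-off on a school-level contrast.**
- REML estimates the variance of school means on k − 2 degrees of freedom, so the true size is 2P(t on k − 2 df > 1.96).
- ML divides by k instead of k − 2, which enlarges the test statistic by √(k/(k − 2)). The true size is 2P(t on k − 2 df > 1.96 × √((k − 2)/k)).

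| Schools | df | REML + z | ML: effective cut-off | ML + z | Correct t cut-off |
|---|---|---|---|---|---|
| 12 | 10 | 7.8% | 1.96 × √(10/12) = 1.789 | 10.4% | 2.228 |
| 10 | 8 | 8.6% | 1.96 × √(8/10) = 1.753 | 11.8% | 2.306 |

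Coverage is one minus size: 92.2% (12 schools, REML) down to 88.2% (10 schools, ML).

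**Check by simulation** (400,000 balanced trials, one comparison of school means, variance component truncated at zero). Cells give size in %.

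| ICC | 12: REML + z | 12: ML + z | 12: REML + t | 10: REML + z | 10: ML + z | 10: REML + t |
|---|---|---|---|---|---|---|
| 0 | 3.95 | 4.43 | 1.96 | 3.92 | 4.50 | 1.57 |
| 0.01 | 6.83 | 8.57 | 4.07 | 6.98 | 8.92 | 3.58 |
| 0.02 | 7.50 | 9.76 | 4.65 | 7.88 | 10.55 | 4.42 |
| 0.05 | 7.82 | 10.32 | 5.01 | 8.56 | 11.69 | 4.95 |
| 0.10 | 7.86 | 10.39 | 4.99 | 8.62 | 11.84 | 5.08 |
| 0.20 | 7.83 | 10.39 | 4.98 | 8.55 | 11.77 | 4.98 |

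The closed form is reached from ICC 0.05 upwards. Below that, truncation at zero makes the test less liberal and, at ICC 0, conservative.

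**Where the hierarchical model is kept.** Under the 10% rule with 12 schools, it survives in about 4% of simulated trials at ICC 0.05, 44% at 0.10, 78% at 0.15 and 92% at 0.20. At ICC 0.10 or more, size among the retained ML fits is 10.4% to 10.5%, so the inflation is at its full value where this model is used.

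**Bonferroni.** If applied over three outcomes (an assumption; the article gives no number), the cut-off is 2.394 for a nominal 1.67%. With 12 schools the true size is 2P(t on 10 df > 2.394) = 3.8% for REML, and with an effective cut-off of 2.185 it is 5.4% for ML. That is 2.3 to 3.2 times nominal.

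**The case against.** The strongest reply is that the article never says z-tests or ML. Naming Stata does not settle it, and a degrees-of-freedom method is often left to an analysis plan, which is not shown here. A reader might infer from the figures that the plan has an 8% to 11% error rate. The documents do not support that: the article is silent on the reference distribution, and the figures are conditional on an uncorrected test. This part of the objection stands. It does not remove the point, because the article does fix the primary model, the software, a threshold for dropping the model, the fallback and the multiplicity method. With 12 clusters the reference distribution matters as much as any of these.

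Second, the main tested term is intervention by time, and a stable school effect cancels from change. This stands too. The figures apply to the arm comparison at post-test. For growth terms, a model with school random intercepts only could have error near 5% or well above 11%, depending on how much schools differ in change over time.

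Third, the 10% rule sends most outcomes with an ICC of 0.01 to 0.05 to single-level analysis, so small-sample error in the hierarchical model seldom arises at those values. This is correct. It limits the point to outcomes that stay in the hierarchical model, or to a plan from which the rule has been removed.

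Two further inferences should be avoided. The hierarchical model is not used for every test, since ANOVA, chi-square, Mann–Whitney and ANCOVA also appear. Ten schools is the required floor, while 10.8 are expected to remain.

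**Conclusion.** The point holds as a recommendation. The primary analysis rests on hierarchical models with 10 to 12 clusters, and no small-sample inference is named. Under a normal reference, a school-level contrast has a true error of 7.8% (REML) to 10.4% (ML) with 12 schools and 8.6% to 11.8% with 10. This assumes uncorrected z-tests, Gaussian outcomes, equal school sizes and an ICC of about 0.05 or more. At ICC 0.01 it is about 7% to 9%, and at 0 there is no inflation. The size of the problem was not derived for the Poisson models or for growth terms. Bonferroni adjustment lowers the nominal level but leaves the per-test inflation in place.

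This is not the largest type I error problem in the section. Single-level tests under the 10% rule have about 14% error at ICC 0.01 and 21% at 0.02, before any covariate adjustment. That needs its own correction.

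**What to change.** State in the analysis section, or in the analysis plan before unblinded data are examined:

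- Linear models are fitted by REML and tested with Kenward-Roger or Satterthwaite degrees of freedom (about schools minus 2), with a school-level random effect for change over time so that interaction terms also use school-level variance.
- Count and binary outcomes are tested with a t reference on schools minus 2 degrees of freedom, or with a permutation test of the school allocation.

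The cost is analysis code and wider intervals. The critical value becomes 2.23 with 12 schools (2.228/1.960 = 1.14 times as wide as REML with z) or 2.31 with 10 (2.306/1.960 = 1.18 times). The t reference is slightly conservative at very low ICC: 4.1% at 0.01 and 2.0% at 0 with 12 schools. Power should be rechecked on this basis. For 0.20 SD at the end of the trial with 12 schools, simulated power under REML falls from 62% with z to 53% with t at ICC 0.01, and from 50% to 40% at 0.02. Part of the power under z comes from its excess error.

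This change does not repair the 10% rule.

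### The main multilevel model compares arms at post-test with no stated baseline adjustment, although the single-level fallback has one; this costs precision, and the form of the growth terms needs fixing too

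*Protocol article*

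**What the plan says.** All of the analysis wording is in the Statistical analysis section of the protocol article.

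- The main test: "mixed effects regression will be used to examine intervention by time interaction effects". Hierarchical models are named as the primary way to examine intervention effects.
- The anchor: "Outcome variables will be centred at post-test to allow for comparisons between groups immediately after the intervention".
- Follow-up: "growth terms will be analysed to determine the magnitude of the follow-up effects". The form of these terms is not given, nor whether the baseline survey is one of the modelled occasions.
- The switch: if "less than 10% of systematic variance exists between school level for any outcome variable, HLM will be abandoned and single-level analyses will be used".
- Baseline adjustment, for the outcomes that are switched: "For these variables, ANCOVAs utilising the SPSS GLM procedure will be conducted to account for any baseline differences that might exist between groups".

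For outcomes that stay in the multilevel model, the only stated use of baseline is a single-level check of equivalence between groups, which adjusts nothing. The Study design section allocates six schools to each arm. The timeline in Table 2 puts baseline, the four lessons and post-test in the same school term, with the last survey two years later.

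**The concern.** The adjustment is attached to the branch that needs it less. Outcomes with a small between-school share go to ANCOVA, where baseline is accounted for. Outcomes with a share of 10% or more stay in the multilevel model, where the post-test contrast is a difference in levels with no stated adjustment. With only six schools per arm, and a large between-school share, the two arms can easily start some distance apart by chance. A reader of the post-test result could not then separate the intervention from the starting gap, although every student's baseline score is collected.

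The growth terms raise a second question. Any immediate effect of four weekly lessons is a step very near the start of a two-year time axis. A smooth curve through baseline and all follow-ups cannot follow a step and then a decline, so it would smear the post-test effect.

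**Working it through.** **Inputs from the article.** Six schools per arm (Study design); 75 students per school ("five schools (with an average of 75 students each) will need to be randomly allocated", Sample size calculations); target difference 0.20 SD at the end of the trial, 80% power, p = 0.05, three occasions, 10% school dropout (same section); surveys at baseline, post-test, 6, 12 and 24 months (Assessment).

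**Assumed inputs.** ICC 0.10 and 0.15; two-sided test; within-student correlation rho; post-test at 1.5 months; the effect profiles below; a baseline gap of 0.10 SD that stays constant over time.

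**1. The plan's own figures.** Schools needed: 10/(1 − 0.10) = 11.1, rounded up to 12, and 12 × 75 = 900. This reproduces. For power, a slope-difference formula with three equally spaced occasions gives schools per arm = 2(1 − rho)(1.96 + 0.84)²/(75 × 2 × 0.10²). This equals 5.0 at rho = 0.522 and 5.23 at rho = 0.5. The stated 80% is therefore consistent with rho of about 0.5, but rho is not given. The fix below does not change the sample size.

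**2. Chance baseline gap.** SD = sqrt[(2/6)(ICC + (1 − ICC)/75)].

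- ICC 0.10: sqrt[(1/3)(0.10 + 0.012)] = sqrt(0.0373) = 0.193. The probability of a gap beyond ±0.10 is 0.60, and beyond ±0.20 it is 0.30.
- ICC 0.15: sqrt[(1/3)(0.15 + 0.0113)] = sqrt(0.0538) = 0.232. The probabilities are 0.67 and 0.39.

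At ICC 0.10 the school component alone is (1/3)(0.10) = 0.0333 of the 0.0373, or 89% of the variance. Most of the gap is therefore a difference between schools, which persists to post-test so far as school differences are stable.

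For comparison, ICC 0.05 and 0.02 give SDs of 0.145 and 0.105. Outcomes at those values would normally go to ANCOVA, which does adjust.

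**3. Where a constant gap goes.** Adding 0.10 to the arm difference at every survey raises the fitted post-test contrast by exactly 0.10 in each unadjusted version tried: 0.114 to 0.214 (linear in months, with baseline), 0.102 to 0.202 (quadratic, with baseline) and 0.185 to 0.285 (linear from post-test on). It adds 0 to the slope in all of them. A fitted difference at 24 months built from the same unadjusted level also moves, from 0.04 to 0.14 in the last version.

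**4. Step then decay.** Assumed true arm differences are 0, 0.20, 0.15, 0.10 and 0.05 SD. With complete data and exchangeable covariance, generalised least squares equals an ordinary fit to these five points.

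- Linear in survey number (−1, 0, 1, 2, 3): the cross-product is −0.20 + 0 + 0.10 + 0.10 = 0, so the slope is 0 and the post-test value is the mean, 0.100.
- Linear in months (0, 1.5, 6, 12, 24; mean 8.7): slope = −0.75/379.8 = −0.002 per month; post-test value = 0.100 + 0.002 × 7.2 = 0.114. The fitted baseline difference is 0.117, where the truth is 0.
- Quadratic: 0.102 (months) or 0.136 (survey number) at post-test.
- Linear from post-test on, baseline left out: 0.185 (months) or 0.200 (survey number), with the decay followed well.

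For a lasting step of 0.20, the linear fit through baseline gives 0.127 (months) or 0.120 (survey number) at post-test, with a spurious rise afterwards. Starting at post-test gives 0.200.

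**The case against.** The strongest reply is that a journal article condenses the plan. Covariate lists and the form of time usually sit in the full protocol or SAP, which are not shown, and their absence is not an error. That stands for the growth terms: the article fixes no straight line through baseline, and reading growth as starting at post-test fits its wording at least as well. The misfit in step 4 is therefore conditional. The reply is weaker for baseline adjustment, because the article does address it and confines it to the switched outcomes.

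Three further points stand.

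- The stated test is the intervention-by-time interaction. If baseline is a modelled occasion, a constant gap cancels from it. What is exposed is the difference in levels at post-test.
- Under randomisation a chance gap is sampling variance, and the school random effect carries it into the standard error. A reader might infer a biased effect; the design does not support that.
- The illustrations are in SD units and suit scores such as knowledge and intentions. They do not describe the drug-use outcomes: under 3% of 14 to 19 year olds report past-year ecstasy use (Background), and counts go to a Poisson model.

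The sentence about centring the outcome is an editorial slip; its stated purpose shows that time is meant.

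**Conclusion.** The point holds in a limited form. As written, the post-test contrast in the multilevel model has no stated baseline adjustment, and the 10% rule keeps that model for the outcomes most exposed to chance imbalance. At an assumed ICC of 0.10 to 0.15, the baseline gap has an SD of 0.19 to 0.23, about as large as the 0.20 effect that the article uses as its target (stated there for the end of the trial). The cost is precision and interpretability, not systematic bias, and the intervention-by-time slope is not affected by a constant gap.

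Under-estimation of an immediate effect (0.20 fitted as about 0.10 to 0.14) arises only if a smooth linear or quadratic trajectory includes the baseline survey. A reader might infer that both the post-test effect and the follow-up slope are distorted whichever model is fitted. The documents do not support that, because the form of growth is open and growth from post-test recovers 0.185 to 0.200.

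The size rests on the assumed ICC, a gap that persists over time, and the assumed effect profiles. Adjusting is an almost free improvement, not the repair of an invalid analysis.

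**What to change.** State one of two specifications for the multilevel model:

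- the four post-baseline surveys as outcomes, with the student's baseline score and its school mean as covariates; or
- all five surveys as outcomes, with the arm difference at baseline constrained to zero.

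In either case treat survey occasion as categorical or, where baseline is modelled, use piecewise growth with a knot at post-test. Report the adjusted arm difference at each follow-up, including the end of the trial, where the power statement applies. Keep the growth terms as a secondary description. Reword the centring sentence so that time, not the outcome, is centred at post-test.

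The cost is a paragraph of analysis text and a few extra parameters. A school-mean covariate uses one of about 12 − 2 = 10 between-school degrees of freedom. No new data are needed.
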